## AIM 1: Mobile WACh EMPOWER RCT

## 12.1 Study Design

The study is a non-blinded cluster randomized controlled trial.

We will conduct a cluster RCT to evaluate a combined counseling intervention (tablet decision-support tool plus SMS for follow-up support) to (counseling and SMS support) on contraceptive discontinuation rates. Cluster RCTs are well-suited to interventions that occur at the clinic, rather than individual level. The randomization at a clinic level allows for the traditional benefits of randomization. We will include a total of 10 clinics in the RCT, 5 receiving standard of care and 5 receiving the intervention and compare contraceptive discontinuation as a primary outcome, and dual method use and unmet need for family planning as secondary outcomes, between the 2 arms.

Randomization procedures:

For the RCT, 10 clinics will be randomized to receive the Mobile WACh Empower intervention or no intervention (SOC). Depending on the heterogeneity of baseline facility factors, restricted randomization may be used to ensure an equal distribution of potentially confounding factors. [name] (Biostatistician) will generate the randomization assignment for each clinic.

Masking procedures: Because this is a clinic-level intervention, there will be no masking procedures.

Detailed Description of Procedures:

5 clinics will be randomized to receive the Mobile WACh Empower intervention and 5 to receive no intervention. Depending on the heterogeneity of baseline facility factors, restricted randomization may be used to ensure an equal distribution of potentially confounding factors such as urban vs. rural site or clinic size. [name] (Biostatistician) will generate the randomization assignment.

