## 12.4 Sample Size Determination

| **Table 3. Number of clusters needed assuming n=300 women per cluster (accounting for up to 10% attrition) 80% power, α=0.05, two-sided testing, coefficient of variation=0.2** | | | | | |
| --- | --- | --- | --- | --- | --- |
| *FP discontinuation* ***Arm 1*** | | | | | |
| **Arm 2** | **20%** | **25%** | **30%** | **35%** | **40%** |
| **45%** | 6 | 8 | 12 | 26 | 103 |
| **50%** | 6 | 6 | 10 | 14 | 32 |
| **55%** | 4 | 6 | 8 | 10 | 18 |
| **60%** | 4 | 6 | 6 | 8 | 12 |

Based on literature ([7](#_ENREF_7)) and recent data among women receiving HIV care in Kenya ([63](#_ENREF_63)) we anticipate 50% of women in the control arm will discontinue FP by 2 years. Assuming α=0.05, 2-sided testing, and a coefficient of variation of 0.2, 10 clinics (5 per arm), and 300 women/clinic we have 80% power to detect a 40% reduction in discontinuation for reasons other than planned pregnancy (30% discontinuation rate) (**Table 3**). Prior data suggest the coefficient of variation falls as cluster size increases, is often ≤0.25, but rarely >0.5; therefore, a coefficient of variation of 0.2 is expected to be adequate. We will enroll 347 women to allow for 10% attrition after enrollment plus additional attrition between consenting and the return visit for use of the counseling tool and completion of enrollment, for a total sample size for analysis of 3300 women. Power was conservatively calculated factoring in potential attrition. With 10 clusters we will also have sufficient power to detect a difference in unmet need for FP (reduction from 25% to 15%) and an increase in dual method use from 40% to 65%.

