**12.5 Statistical analysis** We will compare facility and individual characteristics (accounting for clustering) to determine adequacy of randomization. In the primary intent-to-treat analysis, we will compare time to FP discontinuation (no method use for >1 month, 2 years of follow-up) using Cox-proportional hazards regression, accounting for clustering.([87](#_ENREF_87)) Women not initially on FP at baseline will enter the analysis once initiating FP. We will use Poisson generalized linear models (GLMs) with a log-link function to compare secondary outcomes, an offset of time and robust standard errors to compare rates of dual method use and unmet need for FP between arms accounting for clustering (Table 4). This analytical approach is appropriate for rare outcomes.([88](#_ENREF_88), [89](#_ENREF_89)) We will conduct an exploratory analysis comparing VL suppression (<1000 copies/mL) between arms among women who become pregnant using generalized estimating equations with a log link, exchangeable correlation structure, and clustering by clinic. Additional exploratory analysis comparing unintended pregnancy rates between arms will be done using a Poisson GLM as described above. Data will be disaggregated by age, marital status, fertility plans, FP method and user type (initiator, continuer, or switcher). Although we expect low attrition and no differences in attrition by arms we will assess whether there is selection bias due to attrition by comparing women retained vs. not retained and report any differences. We will use multivariate imputation by chained equations to impute variables with >25% missing values.

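### With five clinics per arm, the robust standard errors fixed for the secondary outcomes exceed two-sided 0.05 unless corrected for few clusters; so does the primary Cox model if it uses an ordinary cluster sandwich

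*Protocol*

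**What the plan says.** Section 12.1 of the protocol sets the number of clusters: "We will include a total of 10 clinics in the RCT, 5 receiving standard of care and 5 receiving the intervention". It adds that restricted randomisation may be used, depending on how much the facilities differ at baseline.

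Section 12.4 gives the planning inputs: "Assuming α=0.05, 2-sided testing, and a coefficient of variation of 0.2, 10 clinics (5 per arm), and 300 women/clinic". The control-arm figure is 50% discontinuation by 2 years, against 30% under the intervention. The stated power is 80%. The section also claims enough power for unmet need (25% to 15%) and dual method use (40% to 65%).

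Section 12.5 gives the analysis. Time to discontinuation is compared "using Cox-proportional hazards regression, accounting for clustering". Table 4 adds only that this is a time-to-first-event Cox analysis. For the secondary outcomes the text is more specific: Poisson models with a log link, an offset for time and "robust standard errors to compare rates of dual method use and unmet need for FP between arms accounting for clustering". Table 4 repeats robust standard errors for both secondary outcomes and for the two exploratory ones. The reason given for the Poisson approach is that it suits rare outcomes. No degrees of freedom, t reference, bias correction, clinic-level test or permutation test is mentioned.

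**The concern.** A cluster-robust variance is justified when there are many clusters. With ten it fails in two ways. It is biased downward, because it uses squared deviations of clinics from their own arm mean without allowing for having estimated that mean. It is also itself a noisy estimate, so a normal reference is too optimistic. Both errors make p-values too small and intervals too narrow.

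A chance imbalance between two groups of five clinics could therefore be reported as an effect on dual method use or unmet need well above the nominal 5% rate. The rarity argument in section 12.5 does not help: it does not concern the number of clusters, and the planned frequencies of 25% and 40% are not rare. For the primary outcome, the unspecified phrase leaves room for the same default.

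**Working it through.** **Inputs from the protocol.** Five clinics per arm; two-sided 0.05; coefficient of variation (CV) 0.2; 300 women per clinic; 50% vs 30% (section 12.4 and Table 3).

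**The plan's own figure.** Table 3 gives 10 clusters for 50% vs 30%. The protocol names no formula. A standard unmatched-cluster formula is

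c = 1 + (1.96 + 0.8416)² × [p0(1−p0)/m + p1(1−p1)/m + CV²(p0² + p1²)] / (p0 − p1)²

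- m = 300: the bracket is 0.46/300 + 0.04 × 0.34 = 0.01513; c = 1 + 7.849 × 0.01513/0.04 = 3.97, so 4 per arm, 8 clusters.
- m = 270 (300 less 10%): the bracket is 0.01530; c = 4.003, so 5 per arm, 10 clusters.
- A version based on the noncentral t gives 10 at both sizes.

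The stated 10 is therefore reachable, but the formula used cannot be identified.

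**False-positive rate, equal clinics.** Within an arm of c clinics, the uncorrected sandwich is Σ(rᵢ − r̄)²/c², while the unbiased variance of the arm mean is Σ(rᵢ − r̄)²/[c(c−1)]. The ratio is (c−1)/c = 4/5. The correctly scaled statistic has about 2 × (5 − 1) = 8 degrees of freedom. A nominal critical value k therefore has true size P(|t₈| > k√0.8), with an extra factor √(10/9) where software multiplies the variance by G/(G−1), G = 10.

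| Variance and reference | Effective cut-off on t₈ | True size |
|---|---|---|
| Uncorrected, z | 1.96 × √0.8 = 1.753 | 11.8% |
| G/(G−1), z | 1.96 × √(0.8 × 10/9) = 1.848 | 10.2% |
| Uncorrected, t₈ | 2.306 × √0.8 = 2.063 | 7.3% |
| G/(G−1), t₉ | 2.262 × √(0.8 × 10/9) = 2.133 | 6.6% |

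CV, clinic size and event rate do not appear in this expression.

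**Simulation check under the null.** 4,000 runs per setting, 10 clinics, about 10% loss over 2 years.

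- Equal clinics, CV 0.1 to 0.3, 150 to 330 women, risk 50% or 25%, uncorrected with z: Cox 11.2-11.8%, Poisson 11.3-11.8%. At CV 0.2 and 300 women, both 11.4%.
- Unequal clinics (CV of clinic size 0.4 and 0.6, an assumption), uncorrected with z: about 13% and 16% for both models.
- Sandwich scaled by 5/4 with t₈, Cox: 4.4-5.1% with equal clinics; 6.1% and 7.5% with unequal ones.
- Clinic-level t-test, 8 degrees of freedom: 4.2-5.0% throughout.

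**Power of the clinic-level t-test.** Noncentral t, 8 degrees of freedom, five per arm, 300 women, noncentrality δ = |p0 − p1|/√(v/5), where v is the bracket above.

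| Contrast | CV 0.2: v, δ, power | CV 0.25: v, δ, power |
|---|---|---|
| 50% vs 30% | 0.01513, 3.64, 88.8% | 0.02278, 2.96, 73.8% |
| 25% vs 15% | 0.00445, 3.35, 83.4% | 0.00636, 2.80, 69.1% |
| 40% vs 65% | 0.02486, 3.55, 87.2% | 0.03796, 2.87, 71.1% |

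**The case against.** The strongest objection concerns the primary outcome. A reader might infer that the planned Cox analysis runs at about 12%. The protocol does not support that: it names no sandwich, frailty term, stratification or reference distribution, and the choice of variance estimator is commonly left to the statistical analysis plan, which is not available here. This stands, so the claim for the Cox model is conditional. A frailty-type model with a z-test would not be a safe way out either: by analogy with a random-intercept model, its size would be about 8.6-11.8%.

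For the secondary outcomes, bias-corrected sandwich estimators are also robust standard errors, so the wording does not exclude a correction. That is fair. The text is incomplete rather than incompatible with the remedy. But it does fix the estimator, in two places, and leaves out the part that decides whether alpha is held.

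A reader might also infer that the sizing assumed a small-sample cluster test and that the analysis contradicts it. That is not supported. No formula is named, and the candidate used above gives 8 clusters, not 10, at Table 3's own 300 women.

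Finally, restricted randomisation was not simulated. Balancing prognostic factors could change the error rate of an unadjusted analysis. This is a reason to match any permutation check to the actual allocation scheme.

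**Conclusion.** The point holds for the secondary outcomes, and conditionally for the primary. If the robust standard errors fixed in section 12.5 and Table 4 are used without a small-sample correction, the false-positive rate at nominal 5% is about 10-12% with a normal reference and equal clinics, and about 6.6-7.3% with a t reference but no adequate bias correction. It rises to about 13-16% with a normal reference if clinic sizes vary as assumed above. The Cox model carries the same rates if it uses an ordinary cluster sandwich with a z-test; the protocol does not say which method it means.

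The equal-clinic figures depend only on the number of clinics, the variance factor and the reference distribution. The unequal-clinic figures rest on assumed size variation, although the candidate sites in section 12.2 range from health centres to district hospitals.

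**What to change.** In section 12.5 and Table 4, state that inference for all Aim 1 outcomes uses a small-sample method:

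- **Preferred:** one summary per clinic (log rate, or log cumulative incidence for discontinuation), compared by a t-test on 8 degrees of freedom.
- **Alternative:** the Cox and Poisson models with a bias-corrected sandwich and about 8 degrees of freedom. The correction should allow for unequal clinics, since simple 5/4 scaling with t₈ still gives about 6-7.5% when sizes differ.
- **Check:** a permutation test over the allocations that any restricted randomisation allows.

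The same text should say what accounting for clustering means in the Cox model.

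No clinics, women or data are added. The cost is wider intervals: with equal clinics, about 2.306/(1.96 × √0.8) = 1.32 times the width given by the uncorrected z method. Power stays above the stated 80% for all three contrasts at CV 0.2, but falls to about 69-74% at CV 0.25. Section 12.4 calls values up to 0.25 common while judging that 0.2 is adequate. That loss belongs to a ten-clinic design; an uncorrected test would hide it, not remove it.

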# 16. STUDY LIMITATIONS

*The intervention will not address all structural barriers to RH,* such as availability of skilled providers; but barriers are expected to be equally distributed by arm and intervention counseling may indirectly alleviate provider-related barriers to RH counseling. Self-reported RH outcomes are subject to *social desirability bias*. To minimize bias we will collect medical record and pharmacy data on FP, pregnancy, and VL. *Threats to internal validity* may exist if temporal changes impact study outcomes; the cRCT design mitigates threats. We will document programmatic changes (i.e., personnel, supplies, stock-outs) and statistically adjust for changes over time if necessary. The *counseling tool relies on batteries*, but tablets last 1-2 days with typical use (6-8 consistent hours) without charging and we will supply back-up batteries. This approach is feasible to implement if the intervention is scaled. If smartphone coverage increases, counseling content could be incorporated into applications designed for use on personal mobile devices outside of clinic settings in future studies. Due to the low incidence of pregnancy (10/100 person-years), *we lack power to determine impact on unintended pregnancies and MTCT in the trial*. We will use mathematical modeling to measure projected health and economic impact of the intervention on these outcomes on a national scale, and provide important updates of cost-effectiveness on reducing on unmet need for FP among WLWH.

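### The primary Cox model names no baseline covariate, while the only adjustment foreseen is an open-ended one for programme changes after randomisation.

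*Protocol*

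**What the plan says.** **Primary model.** Protocol section 12.5 describes an intent-to-treat comparison of time to FP discontinuation "using Cox-proportional hazards regression, accounting for clustering". Table 4 repeats a Cox model for time to first event. Neither place lists a covariate, and neither says that covariates are excluded.

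**Baseline variables.** The same section says "Data will be disaggregated by age, marital status, fertility plans, FP method and user type". That is their only stated analytic use.

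**Baseline comparison.** Facility and individual characteristics are to be compared between arms "to determine adequacy of randomization". No consequence for the model is attached.

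**Restriction.** Section 12.1 says that randomisation may be restricted on factors such as urban or rural site or clinic size. It names no matching term in the analysis. It also states that there is no masking.

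**Programme changes.** Section 16 (Study Limitations) says that changes in personnel, supplies and stock-outs will be documented, and that the investigators will "statistically adjust for changes over time if necessary". It gives no criterion for necessity, no form for the variables, and no indication of which analysis is meant.

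**The concern.** With five clinics per arm, chance imbalance in case mix is expected even when randomisation has worked perfectly. A baseline comparison therefore cannot show whether randomisation was adequate. What protects the estimate is a covariate set fixed in advance. As written, the protocol names variables that could serve, gives them no role in the primary model, and reserves adjustment for factors that arise after randomisation.

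Such adjustment carries two risks. Whether it is necessary can be decided by people who know the allocation and have seen outcomes. And a clinic-level intervention may itself affect the factors concerned: the protocol expects it to shift counselling tasks and relieve provider burden, so staffing need not be independent of arm. Adjusting for a consequence of the intervention can remove part of its effect.

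Power is a secondary matter. Case-mix differences between clinics add to the between-clinic variance, which dominates this design, so baseline covariates might recover some precision.

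**Working it through.** **Inputs (section 12.4).** "Assuming α=0.05, 2-sided testing, and a coefficient of variation of 0.2, 10 clinics (5 per arm), and 300 women/clinic"; "we anticipate 50% of women in the control arm will discontinue FP by 2 years"; "30% discontinuation rate" under intervention; planned power 80%. Taking 10% attrition off 300 gives m = 270 evaluable women per clinic. The protocol does not give the share of variance that baseline covariates explain, so a range is assumed below.

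**Step 1: reproduce the plan's figure.** The unmatched Hayes–Bennett formula per arm is

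c = 1 + (1.960 + 0.842)² × [p0(1−p0)/m + p1(1−p1)/m + k²(p0² + p1²)] / (p0 − p1)².

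With p0 = 0.5, p1 = 0.3, k = 0.2 and m = 270:
- within-clinic term: (0.25 + 0.21)/270 = 0.0017
- between-clinic term: 0.04 × (0.25 + 0.09) = 0.0136
- sum: 0.0153
- c = 1 + 7.849 × 0.0153/0.04 = 4.003, rounded up to 5 per arm, or 10 clinics, as stated.

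The formula at m = 270 matches 19 of the 20 cells of Table 3.

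**Step 2: where the variance lies.** 0.0136/0.0153 = 89% is between clinics and 11% within. Covariates that explain only differences among women in the same clinic act on the small part.

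**Step 3: power with 5 clinics per arm.** The non-centrality is 0.20/√(V/5), referred to a t distribution with 8 df (two-sided critical value 2.306). Each variance component is multiplied by (1 − share explained).

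| Assumption (k = 0.2, m = 270) | V | Power |
|---|---|---|
| No covariates | 0.0153 | 88.5% |
| 30% of within-clinic variance only | 0.0148 | 89.5% |
| 100% of within-clinic variance only (ceiling) | 0.0136 | 91.7% |
| 10% of between-clinic variance only | 0.0139 | 91.1% |
| 25% of between-clinic variance only | 0.0119 | 94.7% |
| One clinic-level term that explains nothing (7 df) | 0.0153 | 87.1% |

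**Step 4: a less favourable clinic variance.** Section 12.4 says that the coefficient of variation is often at most 0.25. At k = 0.25 the between-clinic term is 0.0625 × 0.34 = 0.02125, and power without covariates is 73.5%, below the planned 80%. If covariates explain 25% of between-clinic variance, it is 83.8%.

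These figures compare clinic-level proportions at 2 years, which is the scale of the plan's own calculation. They approximate the Cox test and do not replace a calculation for it.

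**Step 5: the programme-change rule.** No arithmetic applies here. Section 12.1 says no masking; section 16 allows adjustment for post-randomisation clinic factors when judged necessary; section 12.5 names no covariate set. Taken together, they leave the choice of adjustment open after outcomes can be seen. Each clinic-level term entered this way also uses one of 8 degrees of freedom.

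**The case against.** The strongest reply is that a covariate list commonly sits in the SAP, which is not shown. That stands as far as it goes. A reader might infer that the primary model is fixed as unadjusted, but the protocol does not say so; it names no covariate and rules none out.

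A reader might also infer that strong predictors are being discarded and power wasted. The documents do not support this. They give no prognostic strength for any variable, and power on the plan's inputs already exceeds the stated 80%. The larger gains appear only if covariates explain between-clinic variance, for which there is no figure.

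Nor does section 12.5 say that the baseline comparison will decide what is adjusted for. The optional restricted randomisation in section 12.1 is a genuine design-stage answer to imbalance, though it is not guaranteed and has no counterpart in the analysis.

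Finally, the section 16 sentence sits among the limitations and follows a remark that the design itself mitigates temporal threats. It does not assign the adjustment to the primary analysis. It does not exclude it either, and this part of the point does not depend on the SAP's covariate list: the rule is written in the protocol without a criterion or a named analysis.

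**Conclusion.** The point holds in limited form and should be acted on. Followed as written, the protocol forgoes pre-specified control of chance case-mix imbalance and permits discretionary adjustment for factors that arise after randomisation and that the intervention may affect. The main gain from correction is a primary estimate that cannot be steered by the choice of adjustment.

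The power gain is uncertain: about 1 percentage point if covariates explain 30% of within-clinic variance only, and about 3 to 6 points (91% to 95% against 88.5%) if they explain 10% to 25% of between-clinic variance. Those shares are assumptions, with k = 0.2, 270 evaluable women per clinic and 8 df. The stated 10 clinics are not in question here.

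**What to change.** 1. State that the primary Cox model adjusts for a fixed set of individual-level baseline covariates: age, marital status, baseline fertility intention, and FP method or user type. FP method or user type must be recorded before counselling, since a method chosen after counselling is not a baseline variable. The protocol does not say when it is recorded, so this needs confirming. Women who start FP later, and so enter the analysis later, form their own category.
2. Add any factor actually used to restrict randomisation. Include region only if it was one of these, because it costs one of 8 degrees of freedom (88.5% to 87.1% if it explains nothing).
3. Report the model without covariates as a sensitivity analysis.
4. Keep the baseline comparison descriptive, with no role in choosing the model.
5. Confine adjustment for programme changes to a sensitivity analysis with the variables and their form defined in advance.

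The cost is protocol or SAP wording, settled before outcomes are compared by arm, and one further model fit. Provided that method or user type is recorded before counselling, no new data are needed. The hazard ratio becomes conditional on the covariates, and the report should say so.

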## 11.2 Specific Objectives

We will leverage our team’s extensive, interdisciplinary experience on HIV, RH, and mobile health (mHealth) to implement and evaluate the Mobile WACh Empower intervention in a cluster randomized controlled trial (RCT) in the following aims:

**Aim 1:** To determine the effect of the Mobile WACh Empower intervention (counseling and SMS support) on contraceptive discontinuation rates. Secondary outcomes include dual method use and unmet need for FP.

Approach: We will conduct a cluster RCT of Mobile WACh Empower versus the standard of care (SOC) among WLWH seeking HIV care in 10 facilities in Nairobi and western Kenya followed for 2 years.

*Hypothesis: Women in the intervention arm will have lower contraceptive discontinuation rates and unmet need, and higher dual method use at 2 years compared to the SOC arm.*

**Aim 2:** To evaluate acceptability, appropriateness, feasibility, and scalability of Mobile WACh Empower implementation under real-world conditions.

Approach: We will conduct in-depth interviews and focus group discussions (FGDs) at intervention sites with a subset of WLWH enrolled in Aim 1 and site HIV care providers during the trial and at exit. FGDs with WLWH during the trial and at exit will be grounded in behavioral theory (Information-Motivation-Behavior Skills Theory) to determine patient-level intervention acceptability and feasibility. During the trial, IDIs will be conducted with providers as well as FGDs at exit. These will be grounded in implementation science (Consolidated Framework for Implementation Research) to understand health system-level acceptability, appropriateness, feasibility and plan for scalability.

*Hypothesis: The intervention will support women’s fertility and contraceptive choices, improve RH self-efficacy, meet needs for RH counseling and support, and streamline provider workflow and counseling. Readiness and implementation climate needed for scaling Mobile WACh Empower will also be assessed.*

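### Dual method use and unmet need are sized as proportions of 15% to 65% but analysed as rates with an undefined time offset and a rare-outcomes rationale, so the ratio may depart from the one powered

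*Protocol*

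**What the plan says.** Section 12.5 of the protocol compares the two secondary outcomes by a Poisson generalized linear model with a log link, "an offset of time and robust standard errors to compare rates of dual method use and unmet need for FP", accounting for clustering. It then adds: "This analytical approach is appropriate for rare outcomes". It does not say whether the offset time is a fixed 2 years, each woman's follow-up, or time to a first event.

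Three other places describe the same outcomes:

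- **Section 11.2, Aim 1 hypothesis:** the intervention arm is expected to have "lower contraceptive discontinuation rates and unmet need, and higher dual method use at 2 years compared to the SOC arm".
- **Section 12.4:** 10 clusters are said to suffice for "unmet need for FP (reduction from 25% to 15%) and an increase in dual method use from 40% to 65" percent. The sentence gives no time point.
- **Table 4:** unmet need is wanting to prevent pregnancy while not using family planning, assessed quarterly and *at* 2 years. Dual use is using condoms with another modern method, assessed quarterly and *by* 2 years, under a row title that speaks of uptake. Both rows list a log-link Poisson model with robust standard errors and no offset.

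**The concern.** Both indicators are states that a woman can enter and leave. The natural summary of such a state at 2 years is a proportion, and section 12.4 plans on proportions. Section 12.5 instead announces a comparison of rates per unit of time. An analyst following the text could report a prevalence ratio at 24 months, a first-event rate ratio, or status divided by follow-up time, and nothing in the protocol settles which.

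The rate reading also fits the population poorly. Eligibility (Box 2) does not depend on contraceptive use, and section 12.5 itself expects some women to be off contraception at baseline. Some may therefore already have unmet need, or already use dual methods, at enrolment. A first-event rate needs an at-risk population, and none is defined for these outcomes.

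At stake is whether the reported ratio can be read against the planned contrast, and whether the choice among ratios is made before the data are seen. Aim 3 also takes unmet need from this trial into a model built on contraceptive prevalence, so a prevalence is what that model needs.

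**Working it through.** **1. Reproduce the plan's figure.** Section 12.4 gives two-sided α = 0.05, 80% power, coefficient of variation k = 0.2 and n = 300 per clinic. The usual formula for unmatched clusters and proportions is

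c = 1 + (1.96 + 0.84)² × [p0(1−p0)/n + p1(1−p1)/n + k²(p0² + p1²)] / (p0 − p1)²,

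where the squared sum is 7.849 with unrounded normal quantiles.

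- Unmet need, 25% vs 15%: bracket = 0.000625 + 0.000425 + 0.0034 = 0.00445. c = 1 + 7.849 × 0.00445/0.01 = 4.49, so 5 per arm.
- Dual use, 40% vs 65%: bracket = 0.0008 + 0.00076 + 0.0233 = 0.02486. c = 1 + 7.849 × 0.02486/0.0625 = 4.12, so 5 per arm.

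With n = 270 (300 less 10%) the values are 4.58 and 4.14, still 5 per arm. The stated 10 clusters are thus reproduced by treating both outcomes as proportions. The powered ratios are 0.15/0.25 = 0.60 and 0.65/0.40 = 1.625.

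**2. What an offset does.** With an arm term and a log(time) offset, the fitted rate in each arm is total events over total time. With one status per woman,

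ratio = (p1/p0) × (mean time in control / mean time in intervention).

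**3. Time equal or balanced.** If every woman is given 2 years, or follow-up has the same distribution in both arms and is unrelated to outcome, the second factor is 1 and the ratio is the powered one. Simulation with 200,000 women per arm agreed: 0.605 to 0.606, and 1.62 to 1.63.

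**4. Differential loss (assumed).** Suppose 5% of control and 15% of intervention women leave, uniformly between 3 months and 2 years (mean 1.125 years), with status unrelated to leaving.

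- Control mean time: 0.95 × 2 + 0.05 × 1.125 = 1.956 years.
- Intervention mean time: 0.85 × 2 + 0.15 × 1.125 = 1.869 years.
- Factor: 1.956/1.869 = 1.047.
- Unmet need: 0.60 × 1.047 = 0.63. Dual use: 1.625 × 1.047 = 1.70.

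A simulation gave 0.619 and 1.704. Its unmet-need value is slightly low because that run gave 0.591, not 0.60, even without an offset. With the losses reversed the factor is 1.869/1.956 = 0.955, and the ratios are 0.57 and 1.55.

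**5. Person-time to first event (assumed).** With a constant hazard and every woman event-free at the start, the rate ratio that yields the planned 2-year proportions is ln(1−p1)/ln(1−p0).

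- Unmet need: ln(0.85)/ln(0.75) = 0.565.
- Dual use: ln(0.35)/ln(0.60) = 2.06.

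If events are detected only at the 8 quarterly visits, the ratio is [1 − (1−p1)^(1/8)] / [1 − (1−p0)^(1/8)]: 0.57 and 1.99.

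| Meaning of the offset time | Unmet need | Dual use |
|---|---|---|
| None, fixed, or balanced | 0.60 | 1.63 |
| Follow-up, 5% vs 15% loss (assumed) | 0.63 | 1.70 |
| Follow-up, 15% vs 5% loss (assumed) | 0.57 | 1.55 |
| To first event (assumed) | 0.565 | 2.06 |
| To first event, quarterly detection (assumed) | 0.57 | 1.99 |

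**The case against.** The strongest reply is that the offset may be harmless and the model is sound. Much of this stands.

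- Section 12.5 expects low attrition with no difference by arm. Under that expectation, and with time not cut at a first event, the offset changes nothing. A reader might infer that the reported ratio is bound to differ from the powered one; the protocol does not support that.
- A log-link Poisson model with robust standard errors is usable for common outcomes as a prevalence ratio. The rare-outcomes sentence is a wrong reason, not proof of an invalid model. One of the two works cited for it appears, from its title, to concern prevalence rate ratios in cross-sectional data, which fits a prevalence intention.
- The 2.06 needs a first-event analysis, and Table 4 names time to first event only for the primary outcome. It is one scenario, not the plan's stated analysis.
- If quarterly records are modelled over equal intervals, the model gives a ratio of average prevalence over follow-up. That is meaningful, but it is not status at 2 years.
- Table 4 may omit the offset only for brevity.

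A reader might also infer that a woman lost at 3 months with unmet need counts 24/3 = 8 times as much as one observed at 24 months. She does not. The model pools events over person-time, so each contributes one event. Her missing 21 months alter an arm's total of 1,500 × 24 = 36,000 woman-months by about 0.06%.

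It could be said that defining the offset belongs in the statistical analysis plan. Its detail does. But the protocol itself fixes a rate comparison, an offset and a rationale, and these conflict with its own hypothesis, indicators and planning values.

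**Conclusion.** The concern holds as an internal contradiction. Both outcomes are defined as statuses, hypothesised at 2 years and sized as proportions of 15% to 65%, yet analysed as rates with an undefined offset, on a rationale that those figures contradict. For status at 2 years the offset can only be idle or move the estimate off the powered contrast.

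The size is conditional. It is nil if time is fixed or balanced. It is about 5% in the ratio for a 10-point difference in loss between arms. It is largest for dual use under first-event person-time, 2.06 against 1.63. The loss pattern, the constant hazard and the event-free start are assumptions made here, not protocol figures. The 2-year time point for both outcomes comes from the Aim 1 hypothesis, not from the power sentence. The sample size for the two outcomes is unaffected, and the primary outcome is not touched.

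**What to change.** 1. In section 12.5, drop the time offset for dual method use and unmet need. State that status at 2 years will be compared as a prevalence ratio, by log-link Poisson with robust standard errors, accounting for clustering by clinic.
2. Delete the rare-outcomes sentence.
3. Reconcile Table 4's *by* 2 years for dual methods with the *at* 2 years of the Aim 1 hypothesis, and make the row title match the status indicator.
4. If a rate of first uptake is also wanted, report it separately, with a defined at-risk population and a defined time.
5. The exploratory unintended-pregnancy analysis refers back to this model. Pregnancy is an incident event, which section 16 puts at 10 per 100 person-years, so state any offset for it in its own sentence.

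The cost is analysis wording only. Status is already collected quarterly to 2 years, and the number of clinics and women does not change. The change should be made before outcome data are compared by arm.
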